#### Step 2 (Decide)

Guided by the formative research results, the team will meet to discuss what specific intervention activities should be modified to address intersectional stigma. This will include a review of the current intervention activities and discussion of how they can be refined to address intersecting stigmas. In consultation with our civil society partners, we will incorporate these changes into the curriculum, identify gaps/errors in logic and make corrections in preparation to conduct a workshop of the intervention with key reference groups.

#### Step 3 (Administer)

After initial preliminary modifications, we will convene a group of programmatic, scientific and technical experts to review the proposed intersectional stigma modifications to the three interventions. The group will convene in a series of workshops conducted over a period of 4 days and will include individuals with experience in delivering each of the three interventions in their original forms, as well as selected individuals who will conduct the qualitative data collection and analyses in the formative phase. We will leverage online videoconference technology to conduct joint workshop sessions (i.e., stakeholders for HP+, Nyansapo and HIVE^3^) because it is consistent with the concept that the intervention must retain relevance to MSM at all points along the HIV testing pathway, including in the HCF and among their peer-groups. Additionally, we will use online breakout rooms to engage in small group discussions where participants can react to the preliminary modifications presented as well as generate ideas for how to improve the responsiveness of the intervention curricula to addressing intersectional stigma.

#### Step 4 (Produce)

Based on the feedback from the simulation workshop participants and our observations of their engagement with the activities, we will determine what content and approaches to incorporate into the adapted intervention manual and which content and processes to edit or forego. In our decision-making process, informed by the qualitative formative research results, we will give priority consideration to maintaining components that have the highest consistency with scientific literature on intersectional stigma, local cultural relevance, and likelihood to be fun/enjoyable-key requisites for successful intervention uptake.

#### Step 5 (Topic)

We will engage topic experts to review the adapted manual and provide feedback on its congruence with the original intervention and local sociocultural relevance. A copy of each adapted intervention manual will be provided to the principal investigators of the original separate level interventions and be reviewed by experts in intersectional stigma. Partnering organizations will give feedback that is key to the local cultural relevance and intervention implementation.

#### Steps 6 (Integrate) and 7 (Train)

In this step, we will take feedback provided by the topic experts and use it to make final revisions to the intervention manual. We will also produce updated training manuals to standardize training and permit future replication of the intervention in other settings. We will provide comprehensive training to study staff whose roles are dedicated to delivering the intervention. We will develop the training to be multi-faceted to facilitate comprehension and retention of training concepts, using strategies successfully deployed in other HIV prevention research projects.

#### Step 8 (Test)

We will conduct an RCT of the multi-level intervention with a 6-month wait-list control. In each city, we will create two pairs from the 4 HCF sites matched by the number of HIV tests performed in the calendar year 2020. We will randomly assign clinics (enveloped odd/even) within each pair to either receive the HP+ or the wait-list control. MSM will be randomly assigned to receive either Nyansapo and HIVE^3^ or wait-list control. MSM in the intervention group will be asked to follow-up for HIV testing and services at one of the HCFs assigned to the HP+ intervention and the MSM in the wait-list control group will be asked to follow-up at any of the HCFs in wait-list control. Nurses from the intervention HCFs will participate as guest facilitators in one of the Nyansapo sessions and will use that opportunity to reach out to MSM to visit their facility for testing. Our primary hypothesis is that the multi-level intervention will increase uptake of HIV testing among MSM participants. We will use research data collectors to measure frequency of HIV testing among MSM at 3- and 6-months post-intervention using a combination of self-report survey and verification by study nurses (for men who get tested for HIV at participating HCFs.) Our secondary hypothesis is that the multi-level intervention will reduce intersectional stigma that HCF staff convey and that MSM experience in HCFs. We will use research data collectors to administer a survey measuring intersectional stigma 1) in the HCFs at baseline, 3-months post and 6-months post intervention and 2) among MSM at baseline, 3- and 6-months post intervention.

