**Methods:**

We proposed a mixed method study among MSM in Ghana. First, we will develop the intervention protocol using the Convergence Framework, which combines three interventions that were previously implemented separately in Ghana for reducing stigma at the HCF-level, increasing HIV testing at the peer group-level, and increasing peer social support at the individual-level. Then, we will conduct a cluster randomized controlled trial with four pairs of HCFs matched on staff size. HCFs within each pair are randomized to the HCF-level stigma-reduction intervention or control arm. MSM (n = 216) will be randomized to receive the group-level and individual-level interventions or standard of care control arm. MSM will be assigned to receive HIV testing at one of the HCFs that match their study assignment (intervention or control facility). The frequency of HIV testing between MSM in the study arms at 3 and 6 months will be compared, and the predictors of HIV testing uptake at the HCF, peer group and individual-levels will be assessed using multi-level regression models.

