### Study setting

The study will be conducted in eight communities, four each in the Ashanti and Greater Accra regions of Ghana. Accra and Kumasi, the regional capitols, have the highest proportions of MSM living with HIV in the entire country. Furthermore, HIV testing and access to services remain low among MSM in these communities.

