#### MSM

We will recruit MSM using Starfish sampling—a combination or venue-based/time location sampling and peer-referral sampling strategies [59]. We have used both recruitment strategies separately in previous studies; however, recent evidence demonstrates that the Starfish Sampling (combining the two strategies) optimizes the recruitment of yield of populations that are considered hidden. We will conduct face-to-face recruitment through our civil-society partners serving MSM in-house programs and outreach activities. We will also recruit using coupon-based peer-referrals, which are a component of respondent driven sampling (RDS) [60–62]; however, our interest is in recruiting a sufficient sample size of MSM; therefore, we will not apply statistical weights to attempt to generate a population estimate that is the hallmark of the RDS approach. We established region-specific enrollment targets [Accra (n = 108), Ashanti (n = 108)] based on estimation of MSM population sizes in each city. We will employ and train research assistants from outreach staff at our two civil society organizations who already have extensive experience engaging MSM for research and program activities.

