Additionally, multivariable logistic regression will be used to compute the adjusted odds ratio and 95% CI for the binary outcome–HIV testing. The successful uptake of HIV testing can be dependent on the environment in the HCF so that HIV testing among MSM participants at the same HCF may be corrected or “clustered.” To account for the potential post-randomization clustering effect in this individually randomized clinical trial, a generalized linear mixed-effects model with a logit link function will be fitted, and this model includes both HCF cluster-level and MSM individual-level factors. Structural equation modeling will be performed to evaluate the association between the multilevel intervention and uptake of HIV testing while simultaneously assessing the mediation role of intersectional stigma. We will also perform the same analyses for HIV testing within three months of randomization, although the analyses may be underpowered. The likelihood of intervention contamination across the study groups could not be excluded, because some participants may not receive the respective interventions to which they are randomized, e.g., some members of the control group may seek health care at the intervention HCFs during this trial. Therefore, we will also perform per-protocol analysis, which includes only those participants who strictly adhere to the protocol and report the results along with the results of the intention-to-treat analyses. To estimate the effect size of the HP+ intervention for staff, we will compare the rates of willingness to provide healthcare to MSM between the staff in intervention and control HCFs. Chi-square test and t-test will be used for the binary (willingness) and continuous (stigma score) outcomes, respectively. Multivariate logistic or linear regression models will be fitted while adjusting for confounding factors such as sex and job title of the staff.

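### Facilities are randomised in matched pairs within city, but the stated primary and staff tests cannot condition on city or pair, no model names either, and two matching variables are given

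*Protocol article*

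**What the plan says.** **Design.** The Abstract plans "four pairs of HCFs matched on staff size". Step 8 (Test) gives a different rule, applied separately to the two cities: "we will create two pairs from the 4 HCF sites matched by the number of HIV tests performed in the calendar year 2020". On allocation it then states: "We will randomly assign clinics (enveloped odd/even) within each pair to either receive the HP+ or the wait-list control". Study setting places four of the eight communities in each region. Under Recruitment (MSM), enrolment targets are 108 men for Accra and 108 for Ashanti. No stratification is stated for the random assignment of the men, and the Statistical analysis plan section describes the trial as individually randomised, with clustering that arises after randomisation.

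**Analysis.** The same section tests the primary hypothesis with a chi-square statistic without correction. It adds a multivariable logistic regression whose covariates are not listed, and a logistic mixed model with HCF-level and individual-level factors that are not listed either. For staff: "Chi-square test and t-test will be used for the binary (willingness) and continuous (stigma score) outcomes, respectively", followed by regressions that give sex and job title as examples of adjustment factors. City, region and matched pair are named nowhere in the section.

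**The concern.** When randomisation is restricted, the analysis should normally reflect the restriction. Otherwise the variation that the design balanced between arms stays in the error term. Four HCFs per arm leave few degrees of freedom at HCF level, so a real difference between cities could cost noticeable precision in any analysis that treats the HCF as the unit of variation.

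The plan's only explicit trigger for further adjustment is non-equivalence seen at baseline. Pairing within city puts two HCFs of each arm in each city by construction, so for the HCF and staff comparison this trigger would not normally pick up city.

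Separately, staff size and HIV test volume can produce different pairs from the same four HCFs. Pairs are formed before allocation, so the matching variable is part of the randomisation procedure. A reader of the results needs to know which one was used.

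**Working it through.** **Passages side by side.** The Abstract gives staff size as the sole matching variable; Step 8 gives 2020 HIV test counts as the sole matching variable. Matching on both is possible, but neither passage says so.

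**Which analyses could hold city or pair.**
- Primary MSM chi-square: no, as specified.
- Staff chi-square and t-test: no, as specified.
- MSM logistic and mixed models, staff regressions: possible, because the covariate lists are open, but neither factor is named.

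**Plan's own figures.** The plan gives no figure for the precision gained by stratifying. The inputs below come from its Sample size section: control rate 40%, ICC 0.10, and 86 men per arm at six months. The recruitment figure reproduces: 86/0.8 = 107.5, rounded up to 108 per arm, or 216. How the 86 was derived is a separate question; it is used here as stated.

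**Effect of a city term on the width of an HCF-level interval.** Assumptions: four HCFs per arm with equal numbers, so 86/4 = 21.5 men each; the 40% variance, 0.4 × 0.6 = 0.24, in both arms; and an ICC of 0.10 that includes any city component.

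1. Variance of an HCF mean = 0.10 × 0.24 + 0.90 × 0.24/21.5 = 0.024 + 0.010 = 0.034.
2. City share of that variance = (difference/2)² / 0.034.
3. Degrees of freedom fall from 8 − 2 = 6 to 5, so the critical t goes from 2.45 to 2.57, a ratio of 1.05.
4. Width ratio (with city / without) = √(1 − share) × 1.05.

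| City difference in testing | Share | Width ratio |
|---|---|---|
| 0 points | 0 | 1.05 |
| about 11 points | 0.09 | 1.00 |
| 15 points | 0.17 | 0.96 |
| 20 points | 0.29 | 0.88 |

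Step 4 is an approximation. With a fixed city difference, the city part enters the 6-df mean square with weight 8/6. Allowing for that moves break-even to about 10 points and the gains at 15 and 20 points to about 7% and 16%, so the table is slightly cautious.

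**Full pair terms.** These leave 3 df (t = 3.18). They pay off on interval width only if they remove 1 − (2.45/3.18)² = 41% of the HCF-level variance. Power for 70% against 40% points the same way. The pair-matched t-test has 38%, 44%, 52% and 64% power at within-pair correlations of HCF effects of 0, 0.25, 0.5 and 0.75, against 51% for the unpaired cluster t-test. The correlation is not given in the documents, hence the range. A permutation test over four pairs cannot give a two-sided p below 2/16 = 0.125.

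**Direction of the error.** In a simulation under the null (40% rate, ICC 0.10, four HCFs per arm, 22 men each, 20,000 runs), the unpaired cluster t-test rejected in 5%, 2.6% and 1.5% of runs at within-pair correlations of 0, 0.5 and 0.75. Ignoring the pairs is therefore conservative once clustering is handled. The chi-square rejected in 28%, 18% and 11% of runs. That excess comes from ignoring HCF clustering, not from ignoring city or pair.

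**The case against.** - **Silence is not exclusion.** A condensed article commonly leaves covariate lists to the SAP. This stands for the logistic, mixed and staff regression models: a reader might infer that they omit city, and the text does not support that. It does not help the chi-square and t-tests, which are specified in a form that has no place for city or pair.
- **The restriction is stated only for HCFs.** A reader might infer that the men were also randomised within city. The regional figures are enrolment targets, not a rule of allocation, so this is not established. City still matters for the men as the level within which their HCFs were paired.
- **No evidence of a city difference in the outcome.** The Introduction's 34% for Accra and 14% for Kumasi are HIV prevalences, and it is tempting to read them as showing that the cities differ in testing. They do not: the outcome is testing uptake in men reporting negative or unknown status, and the one past-year testing figure pools the two cities. Below about 11 points, the city term costs precision.
- **The benchmark is not the stated primary test.** The chi-square has no HCF-level error term, so the gain applies only to an analysis that already handles clustering. This stands.
- **Matched pairs may be undefined for the men.** Step 8 lets control men attend any control HCF, whereas the Abstract and the confidentiality section speak of one assigned HCF. This stands and limits the pair analysis.
- **The pairing rule is usable.** Step 8 alone can be followed, so the conflict does not make randomisation impossible. It leaves unclear which variable was used.

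**Conclusion.** The point holds in a limited form. The matching variable is contradictory between the Abstract and Step 8. The primary test and the simple staff tests cannot reflect the pairing within city, and no model commits to doing so.

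The consequence is one of efficiency in a clustered analysis: from about 5% wider to about 12% narrower over city differences of 0 to 20 points, under the assumptions above. The sign depends on a testing difference that the documents do not report, and the calculation covers the men only. A reader might infer that leaving out city or pair inflates false positives. It does not; that risk comes from ignoring HCF clustering, which this point neither covers nor cures. Adjusting for city is worth prespecifying because it follows the randomisation and its worst-case cost is small.

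**What to change.** 1. Reconcile the Abstract with Step 8 (Test), and report the matching variable actually used.
2. Name city as a fixed effect in the HCF-clustered model for HIV testing, and in staff models for willingness and stigma score that account for HCF clustering.
3. Prespecify a matched-pair analysis (3 df) as sensitivity only: for staff, and for the men only if each is assigned to a single HCF. The passages on assignment need to agree on that first.

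The cost is wording plus one HCF-level degree of freedom, so an interval at most about 5% wider if the cities do not differ. No change to recruitment or data collection is needed.

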### Sample size

Sample size calculation for MSM participants is based on testing the primary study hypothesis that multi-level intervention will increase the HIV testing rate. Our previous study showed that the 6-month HIV testing rate among MSM was 40%. We hypothesize that this rate will increase to 70% after six months of multi-level intervention. This estimate is based on the evidence from the 3MV trial which showed 81% greater odds of HIV testing in intervention compared to the control group at 6-months and is conservative in comparison to UNAIDS “90-90-90” goals. To determine whether our estimated rate of 70% following interventions is different than the comparison rate of 40% with 80% power and Type I error probability 0.05, while assuming a 10% intra-cluster correlation coefficient, we need 86 MSM participants in each arm, or 172 in two arms by the end of 6-month follow-up. Given a cohort retention rate of 80% (based on retention in previous studies with MSM in Ghana), a total of 216 MSM will be recruited. To evaluate the impact of intervention training on intersectional stigma among staff, we will test whether the training intervention will increase the willingness of HCF staff to provide services to MSM. The historical data shows that the willingness rate is 75%. We expect that the intervention will increase the willingness rate up to at least 90% in the intervention clinic staff, while there is no change in the control group, and we will need 97 staff in each arm, or 194 in total, to achieve 80% power with a 5% Type I error rate.

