## Introduction

In Ghana, men who have sex with men (MSM) are at high risk of HIV acquisition and have low HIV testing rates, often delayed until the point of illness. HIV prevalence among MSM is over eight times higher (18%) than in the general population (2%) [1–4] and higher among MSM in some communities, such as Accra (34%) and Kumasi (14%) [5]. Data on HIV testing among MSM is limited. A 2011 study found two-thirds of MSM in Accra and Kumasi had not been tested for HIV in the past 12 months [3], while a 2012 study found that 40% of MSM respondents had never tested for HIV [6]. Moreover, a qualitative study found infrequent HIV testing practices among MSM due to stigma and inaccurate information [7]; another reported delayed HIV diagnosis, evidenced by reports of having advanced HIV symptoms prior to testing [8, 9].

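### The 70% testing target is attributed to an odds ratio of 1.81, which from 40% gives about 55%; the trial is sized for an odds ratio of 3.5

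*Protocol article*

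**What the plan says.** All the relevant statements are in the Sample size section of the protocol article.

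- Comparison rate: "Our previous study showed that the 6-month HIV testing rate among MSM was 40" per cent.
- Target: "We hypothesize that this rate will increase to 70% after six months of multi-level intervention".
- Source of the target: "This estimate is based on the evidence from the 3MV trial which showed 81% greater odds of HIV testing in intervention", relative to control at six months. The section adds that the estimate "is conservative in comparison to UNAIDS" goals.
- Operating characteristics: "with 80% power and Type I error probability 0.05", "assuming a 10% intra-cluster correlation coefficient".
- Result: 86 men per arm (172 in total) at the end of follow-up, and 216 recruited at 80% retention.

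The Statistical analysis plan section then tests the primary hypothesis with an uncorrected chi-square statistic. The size of the trial is therefore justified by the power of a formal test, and that power depends on the 70%.

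**The concern.** The only effect-size evidence offered for the target is an odds ratio, and the target does not follow from it. Greater odds of 81% is a much smaller change in the testing rate than a move from 40% to 70%. If the combined intervention works about as well as the cited trial suggests, the study has far less than the stated 80% power, and a non-significant primary result would be the likelier outcome. Readers told that power was 80% could take such a result as evidence against the intervention.

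**Working it through.** **Inputs.** From the Sample size section: control rate 0.40, target 0.70, cited odds ratio 1.81, power 80%, alpha 0.05, 86 evaluable per arm, retention 80%. Alpha is taken as two-sided, which the section does not say. The formula is the usual one for two proportions with pooled variance under the null and no continuity correction, which matches the planned uncorrected chi-square test.

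**1. The plan's own figure**

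n = [1.96·√(2·p̄·q̄) + 0.8416·√(p1q1 + p2q2)]² / (p2 − p1)²

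With p1 = 0.40, p2 = 0.70 and p̄ = 0.55: n = (1.96·0.7036 + 0.8416·0.6708)² / 0.09 = 41.97, so 42 per arm before clustering.

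The plan has 86, so the implied design effect is 86/42 = 2.05. No cluster size is stated, so 2.05 is an inference. Under 1 + (m − 1)·0.10 it corresponds to about 11 to 12 men per cluster. The retention step reproduces: 86/0.80 = 107.5, so 108 per arm and 216 in total.

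**2. What an odds ratio of 1.81 gives from 40%**

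- Odds at 0.40: 0.40/0.60 = 0.667
- Times 1.81: 1.207
- Back to a rate: 1.207/2.207 = 0.547, or 54.7%

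**3. What odds ratio 70% versus 40% represents**

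- Odds at 0.70: 0.70/0.30 = 2.333
- 2.333/0.667 = 3.50
- Against the cited figure: 3.50/1.81 = 1.93; on the log scale ln 3.50/ln 1.81 = 2.11. Either way, about twice.

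**4. Could another control rate rescue the link?**

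The largest difference in rates that an odds ratio OR can produce at any control rate is (√OR − 1)/(√OR + 1). For 1.81 this is 0.345/2.345 = 0.147, or 14.7 percentage points. The plan assumes 30 points, so no control rate makes it follow from 1.81.

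**5. Power for 40% versus 54.7%**

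Power = Φ{[(p2 − p1)·√n − 1.96·√(2·p̄·q̄)] / √(p1q1 + p2q2)}, with difference 0.1468, √(2·p̄·q̄) = 0.7061 and √(p1q1 + p2q2) = 0.6984.

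| Effective n per arm | Basis | Power, 40% vs 54.7% | Power, 40% vs 70% |
|---|---|---|---|
| 86 | clustering ignored | 49% | 98% |
| 42 | implied design effect 2.05 | 27% | 80% |

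For the first row: (0.1468·9.274 − 1.384)/0.6984 = −0.03, and Φ(−0.03) = 0.49. For the second: (0.1468·6.481 − 1.384)/0.6984 = −0.62, and Φ(−0.62) = 0.27.

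By the formula in step 1, 80% power for 40% versus 54.7% would need 181 per arm even with clustering ignored, more than twice the planned 86.

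**The case against.** The best defence is that the comparison is not like for like. The 1.81 comes from a single group-level programme. The 70% is hypothesised for a package that adds facility-wide training and peer mentoring, and the Study rationale and aims section argues that single-level interventions fall short. A combined effect above 1.81 is consistent with that reasoning. This part stands: 70% may be a tenable assumption. But the Sample size section does not argue it. It attributes none of the increase to the other two components and says that the figure rests on the cited odds.

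A second defence is that Aim 2 is to gather preliminary data on effect size for a later definitive trial. This also stands, and it lowers the severity. It does not remove the point, because the section still presents 80% power for a formal primary test.

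Four stronger readings are tempting, and the document does not support them.

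- *The target is called conservative against its own evidence.* The text says only that it "is conservative in comparison to UNAIDS" goals. The comparator is a policy benchmark of 90, and 70 is below it. The benchmark is not evidence of an effect, but the wording is not false.
- *The odds ratio was used as a risk ratio.* 0.40 × 1.81 = 72.4% is near 70%, but nothing in the section shows that this step was taken. It is conjecture.
- *The 40% contradicts the Introduction*, which cites a 2011 study in which "two-thirds of MSM in Accra and Kumasi had not been tested for HIV in the past 12 months". The two figures are presented as coming from different studies and cover different periods. They can both be true.
- *The true design effect is 3.05, so power is only 19%.* The abstract describes a "cluster randomized controlled trial with four pairs of HCFs matched on staff size", which gives four facilities per arm, and 1 + (21.5 − 1)·0.10 = 3.05. That assumes 86 men spread evenly over the four. No cluster size is stated, Step 8 (Test) lets control men attend any wait-list facility, and the Statistical analysis plan section describes individual randomization with clustering arising afterwards.

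**Conclusion.** The point holds as an error of derivation. The cited odds ratio corresponds to about 55%, not 70%, and the trial is sized for an odds ratio of 3.5, about twice the only effect-size evidence given. This needs nothing beyond the section's own numbers.

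If the true effect matches that evidence, power is about 49% with clustering ignored and about 27% at the inferred design effect of 2.05, instead of 80%. These figures assume a two-sided 5% test, a control rate of 40% and 86 evaluable men per arm. The 27% also depends on the design effect recovered from 86/42.

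The finding does not show that 70% is unattainable. It shows that 70% has not been justified. It should be fixed, but it is not critical: the correction changes no element of design, conduct or analysis, and a larger trial is already intended.

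**What to change.** Revise the Sample size paragraph in three ways.

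1. State that an odds ratio of 1.81 applied to 40% corresponds to a testing rate of about 55%.
2. Present 70% (odds ratio 3.5) as an assumption about the combined three-level package, with whatever reasoning supports it, and not as a result of the cited trial.
3. Report power at 55% next to power at 70% under the same assumptions, using the design effect actually applied in the calculation. On the figures above that is about 27% and 80% at a design effect of 2.05, or 49% and 98% with clustering ignored.

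The reference to the UNAIDS goals can stay as context, provided that it is not offered as support for the effect size.

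The cost is one rewritten paragraph and a less favourable stated power. No participants are added.

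### The stated 80% power with 86 MSM per arm at ICC 0.10 does not follow from four HCFs per arm; a two-sided cluster-adjusted test would have about 51–66%

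*Protocol article*

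**What the plan says.** The Sample size section sets the number of MSM by a test of the primary hypothesis. The control rate comes from earlier work ("Our previous study showed that the 6-month HIV testing rate among MSM was 40" per cent), and for the intervention "We hypothesize that this rate will increase to 70% after six months of multi-level intervention". The calculation is made "with 80% power and Type I error probability 0.05", and "while assuming a 10% intra-cluster correlation coefficient, we need 86 MSM participants in each arm, or 172 in two arms". Allowing for 80% retention, 216 men are recruited. The section gives no number of clusters, cluster size, design effect or sidedness.

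The layout is given elsewhere. The abstract says "we will conduct a cluster randomized controlled trial with four pairs of HCFs matched on staff size". Step 8 (Test) says "In each city, we will create two pairs from the 4 HCF sites", with one HCF of each pair randomised to HP+ and the other to wait-list control. Both places direct men only to HCFs of their own arm. The Statistical analysis plan section names the HCF as the source of correlation in testing. It tests the primary hypothesis with an uncorrected chi-square and adds a mixed-effects model with HCF-level factors.

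**The concern.** With a fixed, small number of HCFs per arm, an ICC of 0.10 costs far more than a doubling of the unclustered sample size. The article's figure is about double the unclustered requirement, so either the cluster size behind it is not the one in the design, or the number of HCFs did not enter the calculation.

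Two things are at stake. A null result from an analysis that respects clustering would be read against 80% power, although such an analysis would miss a true 30-point difference about 34–49% of the time. In addition, the Discussion says the data will suffice for a larger trial; the same cluster arithmetic carried forward would underpower that trial too.

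**Working it through.** **Inputs.** From Sample size: p1 = 0.40, p2 = 0.70, power 80%, alpha 0.05, ICC 0.10, 86 analysed men per arm, retention 80%. From the abstract and Step 8: eight HCFs, so k = 4 per arm, nested in arm. Assumptions: a two-sided test, because the section asks whether the intervention rate "is different than the comparison rate of 40" per cent; and equal attendance across HCFs.

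**1. Unclustered requirement.** With mean rate 0.55, 2 × 0.55 × 0.45 = 0.495 and 0.40 × 0.60 + 0.70 × 0.30 = 0.45.
- Pooled: n0 = (1.96√0.495 + 0.8416√0.45)² / 0.30² = 41.97, or 42 per arm.
- Unpooled: n0 = 39.2 per arm.

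**2. What 86 implies.** 86 / 41.97 = 2.05. Setting 1 + (m − 1) × 0.10 = 2.05 gives m ≈ 11.5 men per cluster (12.9 from the unpooled formula). The 86 is not reproduced from four HCFs per arm. The retention step is sound: 86 / 0.8 = 107.5, so 108 per arm and 216 in total.

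**3. The documented layout.**
- m = 86 / 4 = 21.5
- Design effect = 1 + 20.5 × 0.10 = 3.05
- Effective n = 86 / 3.05 = 28.2 per arm
- Even with m held at 21.5, 42 × 3.05 ≈ 128 per arm would be needed.

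**4. Power at effective n = 28.2.**
- Pooled z: Φ[(0.30√28.2 − 1.96√0.495) / √0.45] = Φ(0.32) = 62.5%
- Unpooled z: Φ[0.30 / √(0.45/28.2) − 1.96] = Φ(0.415) = 66.1%
- Noncentral t, 2 × 4 − 2 = 6 df: 51.3%

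A beta-binomial simulation (100,000 trials) agrees: 63.2% for a chi-square adjusted by the design effect, and 50.5% for a t-test on HCF proportions.

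**5. The ceiling.** As men are added, effective n = N / [1 + (N/4 − 1) × 0.10] tends to 4 / 0.10 = 40 per arm.
- Pooled z: limit 78.0%
- Unpooled z: limit 80.7%. It reaches 80% at n = 39.244 × 0.9 / (1 − 39.244 × 0.10/4) ≈ 1,870 men per arm.
- t, 6 df: limit 65.7%

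**6. Power over ICC (86 per arm, 4 HCFs per arm).**

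| ICC | Pooled z | t, 6 df |
|---|---|---|
| 0.01 | 95.8% | 88.0% |
| 0.02 | 92.5% | 82.7% |
| 0.03 | 88.6% | 77.6% |
| 0.04 | 84.6% | 72.7% |
| 0.05 | 80.5% | 68.2% |
| 0.07 | 72.6% | 60.4% |
| 0.10 | 62.5% | 51.3% |

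So 80% needs an ICC of about 0.05 or less (pooled z), or about 0.025 or less (t, 6 df).

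**7. The planned chi-square.** In the same simulation at ICC 0.10, the uncorrected chi-square rejects in about 89% of trials under 40% versus 70%, and in about 27% when both rates are 40%. A direct check agrees: 1.96 / √3.05 = 1.12, a two-sided tail of about 26%.

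**The case against.** **Individual randomisation.** The Statistical analysis plan section calls the trial individually randomised, with clustering arising after randomisation. That does not remove the problem. Each HCF serves one arm, so variation between HCFs does not cancel in the comparison, and the article itself assumes an ICC of 10%.

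**Unstated inputs.** The cluster size behind 86 is not given, Step 8 lets control men use any wait-list HCF, and sidedness is not stated. This part stands: equal attendance and a two-sided test are assumptions. A one-sided 5% test gives 74% at 86 per arm, still short, and needs about 170 per arm. If clustering acted in the intervention arm only, power would be about 81%, but the article does not describe that model. Clusters of 11 to 12 men, such as retreat groups, are not described as the clustering unit either. Pair matching might recover some variance, but no gain is quantified and a pair-level analysis would have only 3 df.

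**Pilot purpose.** Aim 2 is to estimate effect size for a later trial, so power is arguably secondary. A pilot need not claim power, but this one does, and the claim does not fit its design.

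**Stronger readings.** A reader might infer that power is 63% at best and that no number of men could reach 80%. Both depend on the formula: unpooled z gives 66% and passes 80% near 1,870 men per arm. A reader might also take 51–66% as the power of the planned primary test. It is not, since that test makes no cluster adjustment. Finally, a reader might conclude that all eight HCFs were counted in each arm. That comes close (86/8 rounds up to 11 men, design effect 2.0, n = 84; power 81.5% at 86), but the article does not say so and 84 is not 86.

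**Conclusion.** The concern holds. The article's own ICC, rates and HCF layout do not give 80% power with 86 men per arm. For a two-sided 5% test that accounts for HCF clustering, power is about 63% by the pooled formula that matches a chi-square, with a range of 51% to 66% across reasonable methods. Further recruitment within four HCFs per arm could not repair this in practice. At ICC 0.10, 86 men per arm reach 80% only with about eight HCFs per arm (81.5%, pooled z) or nine (81.5%, t).

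The result rests on the HCF being the cluster in both arms, roughly equal attendance, and a two-sided test; unequal attendance would lower power further. The uncorrected chi-square does not rescue the claim, because its extra rejections come with a type I error of about 27% against the stated 5%.

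**What to change.** Keep 216 men. In the Sample size section:
- withdraw the statement that 86 per arm gives 80% power at ICC 0.10;
- state the number of HCFs per arm, the cluster size, the design effect and the sidedness used;
- restate power as about 51–66% at ICC 0.10, naming it as the power of a two-sided cluster-adjusted test;
- add a table of power over ICC 0.01–0.10, such as the one above, noting the ICC at which 80% is reached;
- present the trial as estimating the effect size and the ICC, in line with Aim 2.

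The cost is some rewording and a less favourable stated power. No participants or procedures change.
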